## Abstract

**Introduction::**

Evidence has consistently shown the high efficacy of human papillomavirus (HPV) vaccines in preventing cervical cancers. However, the HPV vaccine uptake rate in Hong Kong is very low. We will develop and evaluate an innovative, theory-based multidisciplinary team-led school-based HPV vaccination health-promotion program (MDL-SHPVP), engaging female adolescents, parents/guardians, and secondary school personnel in multicomponent educational strategies and interactive discussions.

**Methods and analysis::**

A cluster randomized controlled trial is proposed. We will recruit 2520 female adolescents and their parents/guardians from 18 secondary day schools. The MDL-SHPVP is underpinned by the Health Belief Model and Precaution Adoption Process Model. Multicomponent interventions will be offered, including education sessions with small group dialogues with a registered nurse and trained healthcare and lay volunteers, and educational computer games. A team of volunteers will be established to raise HPV, cervical cancer, and HPV vaccine awareness. Outcomes include adolescents’ uptake of the HPV vaccine, adolescents’ intention to receive HPV vaccination, vaccine acceptance among parents/guardians, and parents’/guardians’ and adolescents’ HPV knowledge, attitudes, and beliefs. Data will be collected at baseline, 1 month, and 1 year after intervention. The generalized estimating equations analysis will be used for comparing the outcomes between the 2 groups.

**Ethics and dissemination::**

Ethical approval was obtained from the Joint Chinese University of Hong Kong-New Territories East Cluster Clinical Research Ethics Committee (Ref. no.: 2019.055). We will disseminate the study findings via peer-reviewed publications and presentations at relevant events and international and local conferences.

**Trial registration number::**

ClinicalTrials.gov NCT04438291

## Introduction

1

Human papillomavirus (HPV) is the most common sexually transmitted infection, causing genital warts and anogenital cancers. It also causes cervical cancer, the fourth most common cancer in women, with 570,000 new cases reported worldwide in 2018.^[1,2]^ In Hong Kong (HK), cervical cancer has been the seventh most common cancer in women since 2015, and was the ninth leading cause of female cancer deaths in 2016.^[3]^ However, 3 types of HPV vaccines are currently available.^[1]^ Epidemiological studies consistently show the high safety and efficacy of HPV vaccines in preventing 90% of cervical cancers, 82% of high-grade anogenital pre-cancerous lesions, and 90% of genital warts. The protection lasts up to 10 years.^[4–6]^ Since 2007, it has been recommended that all women between 9 and 26 years of age receive HPV vaccines with a regimen of 2 to 3 doses, preferably at an earlier age before becoming sexually active. The highest level of immunogenicity and protection is resulted before exposure to the virus.^[1]^ Evidence has also suggested the potential development of herd immunity in the non-vaccinated population, including men.^[7]^ Nevertheless, a recent global estimate of HPV vaccination coverage among women between 9 and 26 years of age was only 39.7%.^[8]^

Many countries, such as Canada and Australia, have provided government-funded, free national HPV vaccination programs at schools since 2007 for girls aged 12 to 13 years.^[9,10]^ In HK, HPV vaccines are available from local registered physicians, costing HK$1200 to HK$1800 per dose. Teenage girls from low-income families can also join the 3-year Cervical Cancer Vaccination Pilot Scheme, launched in 2016 and supported by the Community Care Fund.^[11]^ Regardless, a systematic review reported an extremely low vaccine uptake rate among HK adolescents (2.4%–9.1%), similar to that in Western countries.^[12]^ Consequently, a new vaccination scheme is offering free HPV vaccination to Primary Five and Primary Six schoolgirls from the academic year, 2018 to 2019.^[13]^ However, current secondary school female adolescents are not covered. Western experiences show that although government-funded HPV vaccination increase the HPV vaccine uptake rate, there exist other barriers hindering adolescents’ or parents/guardians’ decision to initiate and complete HPV vaccination.^[14,15]^ Effective interventions to address these barriers are warranted.

Adolescents’ and parents’ knowledge and attitudes towards HPV and HPV vaccine are crucial in their decision to vaccinate.^[16,17]^ One systematic review of 25 studies found that vaccine uptake among female adolescents was associated with vaccine-related knowledge, attitudes, information provided by healthcare providers, health insurance coverage, age, and childhood vaccination.^[18]^ Another systematic review of 28 qualitative studies and 44 surveys reported the consistent finding that adolescents and parents struggled with their decision due to limited information, declining vaccination for concerns over vaccine safety and low perception of risk of HPV infection.^[19]^ A cross-sectional survey of 1416 female adolescents from 8 secondary schools in HK reported a significant knowledge gap regarding cervical cancer prevention. The 3 most significant factors influencing vaccination include the perception of cancer as a terrifying disease, the provision of more information on cancer prevention from schools and comments from vaccinated relatives and friends. The cost of vaccination and socio-economic background were not significant.^[20]^ Another review also highlighted that perceived beliefs of peers and significant others are associated with HPV vaccination.^[21]^

Previous studies have examined various educational interventions enhancing HPV vaccination uptake. A systematic review of 33 studies found that various educational interventions directed at adolescents or young adults, or their parents increased knowledge, positive intentions, and attitudes. However, they did not lead to an increased rate of HPV vaccine uptake as the rise in the rate of intention was extinguished after 1 month. The review further found a lack of educational interventions explicitly underpinned by theoretical frameworks.^[22]^ A cluster randomized controlled trial (RCT) of 832 students from 18 upper secondary schools in Sweden revealed that a school-based educational intervention underpinned by the Health Belief Model (HBM) resulted in a significantly greater proportion of students in the intervention group deciding to receive HPV vaccination. Significant improvements in condom use and the HBM total susceptibility and severity scores were also seen in the intervention group relative to the control group.^[23]^ Another study of 383 undergraduate students adopted the Precaution Adoption Process Model (PAPM) and found that most unvaccinated students were in the early stages of decision-making regarding vaccination. They perceived low susceptibility of themselves to HPV, but had basic knowledge about HPV. The study suggested that it would be helpful to provide prompts from healthcare providers and education on susceptibility according to students’ stages of decision-making to enhance vaccination rates.^[24]^

Additionally, 2 HK studies reported the effects of educational interventions on HPV uptake and intention. A pre-post study of 953 female adolescents found an 11.3% increase in the number of participants intending to receive HPV vaccination after school-based cervical cancer education underpinned by theories of persuasion. Participants also showed greater knowledge in and a more positive attitude towards HPV vaccination.^[25]^ Another non-profit-funded school-based program using HBM provided free HPV vaccination and educational interventions to 1229 female adolescents (9–14 years) from low-income families. Promising results indicated overall vaccine uptake rates of 81.4% and 80.8% for the first and second doses, respectively. The results showed an association between parents who did not want their daughters vaccinated and inadequate knowledge regarding the vaccine.^[17]^

It is evident that providing sufficient knowledge and conveying positive attitudes towards HPV vaccination among adolescents and their parents/guardians are very important in increasing the HPV vaccine uptake rate. Educational interventions involve a complex design and evaluation driven by theoretical premises crucial to better understanding causal intervention mechanisms and changes in outcomes.^[26]^ The only HK study in which an intervention was developed on the basis of HBM was a one-group pre/post-test study.^[17]^ Further evaluation using a RCT is needed to demonstrate intervention effects on actual vaccine uptake instead of simply on intention to be vaccinated. Furthermore, although previous studies targeted adolescents and/or parents, it would be more comprehensive to include school personnel to better equip them to provide health information to students. Partnerships are needed between schools, students, and healthcare professionals. With the government's introduction of a free HPV vaccination program for primary school girls, the provision of educational interventions for them is obviously necessary. However, it is important to provide the same interventions to secondary school female adolescents requiring catch-up doses. Booster doses of educational interventions are also needed in view of the decreasing uptake rate of the second and third HPV vaccines observed in previous studies. Studies have supported the feasibility of conveying information via volunteers. Hence, more strengthening strategies, including examining the feasibility of training a team of healthcare and lay volunteers for community capacity building to sustain vaccination uptake, are needed.

## Methods

2

### Study design

2.1

A cluster RCT is proposed.

### Objectives

2.2

The study aims to examine the effects of a multidisciplinary team-led school-based HPV vaccination health-promotion program (MDL-SHPVP) on female adolescents and their parents or guardians. The primary outcome is female adolescents’ uptake of the HPV vaccine 1 year after intervention. The secondary outcomes are female adolescents’ intention to receive HPV vaccination, vaccine acceptance among their parents/guardians, and parents/guardians’ and female adolescents’ HPV knowledge, attitudes, and beliefs (from baseline to 1 month after intervention).

### Participants

2.3

We will recruit 2520 adolescents and their parents/guardians from 18 secondary day schools (out of 471 secondary schools). Six schools will be randomly selected from each of the 3 regions of HK (HK Island, Kowloon, and New Territories) using a sample frame compiled from the school lists by district available at the Education Bureau. Adolescents admitted to the trial will be 14- to 17-year-old secondary school female students (seventh to eleventh grade) who have not received an HPV vaccine. Exclusion criteria will include: history of severe life-threatening allergies to a previous dose of HPV vaccine or vaccine component; history of immediate hypersensitivity to yeast; moderate or severe acute illness^[27]^; and participation in previous trials related to HPV vaccination. Only 1 daughter from each family will be selected. Parents/guardians admitted to the trial must have a daughter meeting the above criteria; live with their daughter and spend the most time caring for her; be able to communicate in Chinese; and be willing to attend education sessions. Parents/guardians will be excluded if they currently suffer from psychiatric illness.

### Sample size estimation

2.4

Sample size is estimated based on the primary outcome of the HPV vaccine uptake rate. Several studies have revealed the low uptake rate of HPV vaccine (<10%) in HK.^[20,28,29]^ We anticipate that our proposed MDL-SHPVP can double the uptake rate, and have therefore set this target to determine its effectiveness a priori. We used the power analysis software PASS 14 (NCSS, Kaysville, UT) to estimate that a sample size of 266 participants in the intervention and control groups will be required to achieve 80% power at a 2-sided 5% level of significance to detect a net difference of at least 10% in the uptake rate between the 2 groups, assuming that the rate is 10% for the control group. To allow for an attrition rate of up to 20%, a total of 666 participants with 333 in each group are needed. Furthermore, to account for clustering design, a variance inflation factor, namely the design effect, must be imposed.^[30]^ The design effect is given by 1 + (*m*–1)∗ICC, where *m* is the average cluster size and ICC is the intracluster correlation coefficient of the underlying outcome. A synthesis study revealed that the ICC tends to be small in primary care research, with a median of 0.005 and an inter-quartile range of 0.000 to 0.021.^[31]^ As we do not have empirical data to estimate the ICC for the outcome, we account for an ICC of up to 0.02. By this standard, a total of 18 schools with at least 140 female adolescents from each school will be required.

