### Cluster randomization

2.5

Randomization will be performed at the school level (cluster) rather than the individual participant level to avoid contamination between the intervention and control groups. Schools will be randomized to either the intervention or control group in a 1:1 ratio. All eligible adolescents recruited from the same school will be allocated to either the intervention or control group. Group allocation will be concealed from outcome assessors and the investigators, and performed according to a random sequence generated by an independent statistician using computer-based randomization.

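### The 266 per group stated for 80% power is the 90% power figure; 80% needs 199, so 2520 does not match the stated power (a conservative error)

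*Protocol article*

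**What the plan says.** All the inputs are in the protocol article, almost all of them in section 2.4 (Sample size estimation).

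- Power and significance level: "80% power at a 2-sided 5% level of significance".
- Control uptake: "assuming that the rate is 10% for the control group".
- Effect: the sample is sized "to detect a net difference of at least 10% in the uptake rate between the 2 groups". The text expects uptake to double, so the comparison is 10% with 20%.
- Result before attrition and clustering: "a sample size of 266 participants in the intervention and control groups will be required to achieve 80% power at a 2-sided 5% level".
- Allocation, from section 2.5 (Cluster randomization): "Schools will be randomized to either the intervention or control group in a 1:1 ratio".

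Section 2.4 then allows for 20% attrition (333 per group, 666 in total). It applies a design effect of 1 + (m - 1) x ICC with an ICC of 0.02 and concludes that "a total of 18 schools with at least 140 female adolescents from each school will be required". Section 2.3 (Participants) gives the resulting total of 2520. No 90% power figure appears anywhere in the article.

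**The concern.** Sample size, power, significance level and effect are stated together, and any three of them fix the fourth. Here the four do not agree: 266 per group is about a third more than 80% power needs. Attrition and clustering cannot explain the excess, because the text applies both after reaching 266.

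Two things are at stake. First, the article presents 18 schools of 140 as the number needed for 80% power, which is a claim about burden and resources: 2520 girls, each with a parent or guardian, and five sessions of 28 in each intervention school. Second, the power claim is what a reader uses to judge how much room the trial has if assumptions fail. Section 2.4 says there are no empirical data on the ICC for this outcome, so that margin matters, and as written it is understated.

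**Working it through.** **Inputs.** p1 = 0.10, p2 = 0.20, mean 0.15, difference 0.10, two-sided 5% (z = 1.960), 1:1 allocation. z for power is 0.8416 at 80% and 1.2816 at 90%.

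**Formula (pooled two-proportion z test).**

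n per group = [1.960 x sqrt(2 x 0.15 x 0.85) + z_power x sqrt(0.10 x 0.90 + 0.20 x 0.80)]² / 0.10²

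The first term is 1.960 x sqrt(0.255) = 0.9897. The second is z_power x sqrt(0.25) = z_power x 0.5.

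- 80% power: (0.9897 + 0.4208)² / 0.01 = 198.96, so 199.
- 90% power: (0.9897 + 0.6408)² / 0.01 = 265.86, so **266**, the protocol's figure.

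In the other direction, power = Φ[(0.10 x sqrt(n) - 0.9897) / 0.5]. This gives 0.800 at n = 199 and 0.900 at n = 266.

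**Other standard methods, n per group.**

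| Method | 80% power | 90% power |
|---|---|---|
| Pooled z | 199 | 266 |
| Unpooled z | 197 | 263 |
| Arcsine | 195 | 261 |
| Logit Wald | 208 | 278 |
| Pooled z, continuity-corrected | 219 | 286 |
| Pooled z, one-sided | 157 | 217 |

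Fisher's exact test has power 0.812 at 219 per group and 0.882 at 266. No variant comes near 266 at 80% power.

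**Later steps, starting from 266.**

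- Attrition: 266 / 0.8 = 332.5, so 333 per group and 666 in total.
- Design effect: 1 + (140 - 1) x 0.02 = 3.78.
- Total: 666 x 3.78 = 2,517; 2,517 / 140 = 17.98, so 18 schools and 18 x 140 = 2520.

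These steps all reproduce. As a check in reverse, 9 schools x 112 completers = 1,008 per arm; 1,008 / 3.78 = 266.7 effective per arm; power 0.90.

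**The same steps, starting from 199.**

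- Attrition: 199 / 0.8 = 248.75, so 249 per group and 498 in total.
- Keeping 140 per school: 498 x 3.78 = 1,882; 1,882 / 140 = 13.4, so 14 schools (7 per arm) and 14 x 140 = 1,960. The planned 2520 is 1.3 times this.
- Keeping 18 schools: solve 18m = 498 x (0.98 + 0.02m), giving m = 60.7, so 61 per school and 18 x 61 = 1,098. The planned 2520 is 2.3 times this.

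**Sensitivity, on assumptions that the protocol does not make.** Take equal cluster sizes, 112 analysed girls per school, the design effect recomputed at 112, unpooled variance and a t reference on 16 degrees of freedom.

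- ICC 0.02: design effect 1 + 111 x 0.02 = 3.22; effective n = 1,008 / 3.22 = 313 per arm; power about 91%.
- ICC 0.03: design effect 4.33; effective n = 1,008 / 4.33 = 233 per arm; power about 82%.

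**The case against.** The strongest reply is that nothing is put at risk. The error is conservative: on the protocol's assumptions the trial exceeds the power it claims. The analysis, the type I error and the interpretation of the result are untouched. The interventions are educational, and correcting the text may take one sentence. All of this stands, and it is why the point is not a must-fix.

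Three stronger readings are tempting, and the documents do not support them.

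- A reader might infer that only the power label is wrong, because 266 matches 90% exactly. That is plausible, but it remains an inference. It is also possible that 80% was meant and the wrong n was taken from the software.
- A reader might infer that the trial is 2.3 times too large. That ratio holds only if 18 schools are kept and the number per school is cut. Section 2.6 plans five sessions of 28 adolescents, which is exactly 140 per school, so keeping 140 is at least as faithful to the plan. The ratio is then about 1.3.
- A reader might infer that the trial is underpowered or its size unsafe. The calculation shows the opposite on the stated assumptions.

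The sensitivity figures rest on assumptions that the article does not state, such as equal cluster sizes, although it speaks of an average cluster size. Unequal school sizes would lower them somewhat. A condensed article need not carry them.

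**Conclusion.** The point holds as a wrong pairing of sample size and power. Given 10% against 20% uptake at two-sided 5%, 80% power needs 199 per group (219 with continuity correction), and 266 is the 90% figure under the pooled test. The attrition and design-effect steps are correct, so 2520 carries about 90% power under the protocol's own ICC of 0.02, 20% attrition and 140 per school.

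The trial is not underpowered on those assumptions, but 2520 is not the number that 80% power requires. That number lies between about 1,100 and 1,960 girls, depending on whether the number of schools or the number per school is held fixed. Which of the two stated figures was the slip cannot be settled from the article. Severity: a should-fix correction of a stated power figure.

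**What to change.** Check the saved output of the sample size software and state in section 2.4 which power was intended.

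- If 90%: keep 18 schools of 140 and restate that 266 per group gives 90% power. This costs one sentence and leaves recruitment unchanged.
- If 80%: replace 266 with 199 and recompute the attrition step (249 per group, 498 in total), the design effect, and the number of schools and girls per school. The total of 2520 in section 2.3 and the abstract, and the session numbers in section 2.6, would then need to be brought into line. This costs more, since it reopens the recruitment plan.

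Optionally, add a sensitivity line: with 112 analysed per school, equal cluster sizes and 16 degrees of freedom, power is about 91% at an ICC of 0.02 and about 82% at 0.03. Label these as added assumptions.

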### Cluster randomization

2.5

Randomization will be performed at the school level (cluster) rather than the individual participant level to avoid contamination between the intervention and control groups. Schools will be randomized to either the intervention or control group in a 1:1 ratio. All eligible adolescents recruited from the same school will be allocated to either the intervention or control group. Group allocation will be concealed from outcome assessors and the investigators, and performed according to a random sequence generated by an independent statistician using computer-based randomization.

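### Schools are sampled six per region, but no regional stratification of the 1:1 allocation is described and the analysis names no region term; adding both would cost little

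*Protocol article*

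**What the plan says.** - **Sampling (section 2.3, Participants).** "Six schools will be randomly selected from each of the 3 regions of HK", which gives 18 schools in three equal groups.
- **Allocation (section 2.5, Cluster randomization).** "Randomization will be performed at the school level (cluster) rather than the individual participant level". "Schools will be randomized to either the intervention or control group in a 1:1 ratio". Allocation is "performed according to a random sequence generated by an independent statistician using computer-based randomization". The section gives the unit, ratio, generator and concealment. It mentions no stratification, blocking, matching or other constraint, and it does not say that the sequence is unrestricted.
- **Analysis (section 2.10, Data analysis).** Primary and secondary outcomes are compared by GEE with a correction for the small number of clusters. Region is not named as a covariate.
- **Planning values (section 2.4, Sample size estimation).** ICC up to 0.02, with a cited median of 0.005; at least 140 girls per school; attrition up to 20%.

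**The concern.** The sampling creates three strata of six schools, and six divides exactly into three and three. Read as written, the allocation does not use this structure, and neither does the model. The plan recognises in section 2.10 that the number of clusters is small, which is the setting in which restricting the allocation helps most.

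Two things are at stake. The first is precision: any difference in uptake between regions stays in the error of the treatment comparison, and recruiting 2520 girls does not average it away, because it lies between schools. The second is credibility: a result with, say, five of six Kowloon schools in one arm invites a challenge that could have been prevented.

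**Working it through.** **1. The plan's own cluster count.** The article gives no figure for regional balance. Its number of schools does follow from its inputs: design effect 1 + (140 − 1) × 0.02 = 3.78; 666 × 3.78 = 2517.5; 2517.5 / 140 = 17.98, so 18 schools and 18 × 140 = 2520 girls. (The starting figure of 266 per group corresponds to 90% power for 10% against 20%, not the stated 80%, which needs 199. That is a separate matter and does not enter below.)

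**2. Regional balance without restriction.** Read 1:1 as nine schools per arm. There are C(18,9) = 48,620 equally likely allocations. With a schools of a region in the intervention arm, each region contributes C(6,a) = 1, 6, 15, 20, 15, 6, 1 for a = 0 to 6, and the three values of a sum to 9.

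| Worst regional split | Patterns (intervention schools per region) | Allocations | Share |
|---|---|---|---|
| 3:3 | (3,3,3): 20³ | 8,000 | 16.5% |
| 4:2 | (2,3,4): 6 × 15 × 20 × 15 | 27,000 | 55.5% |
| 5:1 | (1,3,5): 6 × 6 × 20 × 6 = 4,320; (1,4,4) and (5,2,2): 3 × 6 × 15 × 15 = 4,050 each | 12,420 | 25.5% |
| 6:0 | (0,3,6): 6 × 20 = 120; (0,4,5) and (6,1,2): 6 × 15 × 6 = 540 each | 1,200 | 2.5% |

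The counts add to 48,620. Some imbalance occurs in 83.5% of draws, and 5:1 or worse in 13,620 / 48,620 = 28.0%.

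**3. What imbalance could do to the arm difference.** This needs uptake by region, which the article does not give, so the rates here are assumptions. For a 9:9 draw the variance of the chance difference is S² × (1/9 + 1/9), with S² the variance of the regional rates over the 18 schools.
- Uptake 8, 10 and 12%: S² = 12 × 0.02² / 17 = 0.000282; SD 0.8 points.
- Uptake 5, 10 and 15%: S² = 12 × 0.05² / 17 = 0.00176; SD 2.0 points.

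The target difference is 10 points.

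**4. Gain from stratifying and fitting region.** Completers per school: 140 × 0.8 = 112. The between-school share of the variance of a school mean is ICC / (ICC + (1 − ICC)/112).
- ICC 0.02: 0.02 / (0.02 + 0.00875) = 0.696.
- ICC 0.005: 0.005 / (0.005 + 0.00888) = 0.360.

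If region explains a share s of the between-school variance, the variance of the effect falls by about s × that figure.

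| Assumed s | ICC 0.02 | ICC 0.005 |
|---|---|---|
| 0.20 | 13.9% | 7.2% |
| 0.30 | 20.9% | 10.8% |

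**5. Cost.** Take a t reference on clusters less parameters (an assumption; the article names no degrees-of-freedom rule). Two region parameters move 16 df to 14, and the critical value from 2.120 to 2.145. The ratio is 1.012, so intervals are about 1.2% wider, or about 2.4% in squared terms. Break-even needs a variance cut of 1 − (2.120/2.145)² = 2.3%, that is s = 0.023 / 0.696 = 3.3% at ICC 0.02 or 0.023 / 0.360 = 6.4% at ICC 0.005.

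**6. Fitting region without stratifying.** With equal school sizes and region in the model, information on the arm effect is proportional to the sum of a(6 − a)/6 over regions. For 3:3 throughout it is 3 × 9/6 = 4.50. For 4:2, 3:3, 2:4 it is 8/6 + 9/6 + 8/6 = 4.17, or 7% less. For 5:1, 3:3, 1:5 it is 5/6 + 9/6 + 5/6 = 3.17, or 30% less. Adjustment alone therefore does not replace a balanced allocation.

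**The case against.** **The article is condensed and silent, not explicit.** Restriction of the sequence and model covariates may sit in the full protocol or analysis plan. A reader might infer that the trial definitely randomizes without regard to region; the article does not say that. What stands is that section 2.5 sets out the method in some detail, section 2.12 reports adherence to SPIRIT, and region is absent from both the allocation and the model. Unstratified allocation is the natural reading, though not a stated fact.

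**Chance imbalance is not bias.** A reader might infer that region would be confounded with the intervention in a way that invalidates the result. It would not: under randomization the estimate is unbiased in expectation, and between-region variation is part of the between-school variance that the small-sample-corrected GEE is meant to reflect. Section 2.4 also sizes the trial for an ICC of 0.02 without credit for stratification. This objection is right, and it limits the point to precision and credibility.

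**Nothing in the article shows that region predicts uptake.** A reader might infer that region stands in for income, given the price per dose in the Introduction. The same Introduction describes a funded scheme for girls from low-income families, and cites a Hong Kong survey of 1416 girls in which neither cost nor socio-economic background was a significant factor. The income argument is therefore not supported and is not used here. What survives is that the investigators chose to balance their sample on region, and that break-even needs only a small share.

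**Most imbalance is mild.** In 72.0% of equal draws (16.5% + 55.5%) no region is worse than 4:2. It would be wrong to call a marked imbalance likely; its probability is 28.0%.

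**Conclusion.** The point holds as a design improvement; it is not an error that invalidates the trial. The plan builds three equal regional strata and describes neither an allocation nor a model that uses them. Without restriction, exact regional balance has a 16.5% chance and a split of 5:1 or worse a 28.0% chance, assuming nine schools per arm. A reader might go further and infer coin-tossing, with unequal arms as well; the 1:1 ratio does not suggest that, and nothing here depends on it.

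The balance figures rest only on the school counts. The precision gain of 14 to 21% (ICC 0.02) or 7 to 11% (ICC 0.005) rests on an assumed regional share of 20 to 30% of between-school variance. If region explains nothing, the change costs about 1.2% in interval width. That asymmetry, with break-even at a share of roughly 3 to 6%, is the reason to make the change.

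**What to change.** - **Section 2.5:** state that schools are allocated within region, three to intervention and three to control among the six schools of each region. The independent statistician prepares three short lists instead of one, which leaves 20³ = 8,000 possible allocations.
- **Section 2.10:** include region as a fixed effect in the GEE for primary and secondary outcomes. The two changes belong together: stratifying without fitting region leaves between-region variance in the standard error.
- If the full protocol already stratifies by region, say so in section 2.5 and name the matching model term.
- If schools have already been allocated without restriction, the model term can still be specified before outcome data are seen, with the loss of information shown in step 6 of the working.

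The cost is a sentence in each section, two model parameters and no added schools.
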